## Visit 8: ROLAND-MORRIS DISABILITY QUESTIONNAIRE

*To be completed by assessment team investigator*

**Directions:** When your back hurts, you may find it difficult to do some of the things you normally do. Listed below are some sentences that others have used to describe themselves when they have back pain. When you read them, you may find that some stand out because they describe you *today*. As you read the list, think of yourself *today*. When you read a sentence that describes you today, circle YES. If the sentence does not describe you today, circle NO. Remember, only answer YES if you are sure the sentence describes you *today*.

|    |                                                                                      |     |    |
|----|--------------------------------------------------------------------------------------|-----|----|
| 1  | I stay at home most of the time because of my back                                   | YES | NO |
| 2  | I change positions frequently to try to get my back comfortable                      | YES | NO |
| 3  | I walk more slowly than usual because of my back                                     | YES | NO |
| 4  | Because of my back, I am not doing any of the jobs I usually do around the house     | YES | NO |
| 5  | Because of my back, I use a handrail to get upstairs                                 | YES | NO |
| 6  | Because of my back, I lie down to rest more often                                    | YES | NO |
| 7  | Because of my back, I have to hold on to something to get out of an easy chair       | YES | NO |
| 8  | Because of my back, I try to get other people to do things for me                    | YES | NO |
| 9  | I get dressed more slowly than usual because of my back                              | YES | NO |
| 10 | I can only stand up for short periods of time because of my back                     | YES | NO |
| 11 | Because of my back, I try not to bend or kneel down                                  | YES | NO |
| 12 | I find it difficult to get out of a chair because of my back                         | YES | NO |
| 13 | My back is painful almost all of the time                                            | YES | NO |
| 14 | I find it difficult to turn over in bed because of my back                           | YES | NO |
| 15 | My appetite is not very good because of my back pain                                 | YES | NO |
| 16 | I have trouble putting on my socks (or stockings) because of the pain in my back     | YES | NO |
| 17 | I only walk short distances because of my back pain                                  | YES | NO |
| 18 | I sleep less well because of my back                                                 | YES | NO |
| 19 | Because of my back pain, I get dressed with help from someone else                   | YES | NO |
| 20 | I sit down for most of the day because of my back                                    | YES | NO |
| 21 | I avoid heavy jobs around the house because of my back                               | YES | NO |
| 22 | Because of my back pain, I am more irritable and bad tempered with people than usual | YES | NO |
| 23 | Because of my back, I go upstairs more slowly than usual                             | YES | NO |
| 24 | I stay in bed most of the time because of my back                                    | YES | NO |

Score: \_\_\_\_\_

**Investigator Signature:** \_\_\_\_\_

**Date:** \_\_\_\_\_

DAY-MONTH-YEAR

Participant ID # \_\_\_\_\_

Visit Date \_\_\_\_/\_\_\_\_/\_\_\_\_

## Visit 8: PROMIS – PAIN INTENSITY

*To be completed by assessment team investigator*

**Instructions:** Please respond to each item by marking one box per row.

In the past 7 days...

|                                         | Had no
pain | Mild | Moderate | Severe | Very
Severe |
|-----------------------------------------|----------------|------|----------|--------|----------------|
| How intense was your pain at its worst? |                |      |          |        |                |
| How intense was your average pain?      |                |      |          |        |                |
| What is your level of pain right now?   |                |      |          |        |                |

Score: \_\_\_\_\_

**Investigator Signature:** \_\_\_\_\_

**Date:** \_\_\_\_\_

DAY-MONTH-YEAR

Participant ID # \_\_\_\_\_

Visit Date \_\_\_\_/\_\_\_\_/\_\_\_\_

## Visit 8: PROMIS – PAIN BEHAVIOR

*To be completed by assessment team investigator*

**Instructions:** Please respond to each item by marking one box per row.

In the past 7 days...

|                                                        | Had no
pain | Never | Rarely | Sometimes | Often | Always |
|--------------------------------------------------------|----------------|-------|--------|-----------|-------|--------|
| When I was in pain I became irritable                  |                |       |        |           |       |        |
| When I was in pain I grimaced                          |                |       |        |           |       |        |
| When I was in pain I moved extremely slowly            |                |       |        |           |       |        |
| When I was in pain I moved stiffly                     |                |       |        |           |       |        |
| When I was in pain I called out for someone to help me |                |       |        |           |       |        |
| When I was in pain I isolated myself from others       |                |       |        |           |       |        |
| When I was in pain I thrashed                          |                |       |        |           |       |        |

Score: \_\_\_\_\_

**Investigator Signature:** \_\_\_\_\_

**Date:** \_\_\_\_\_

DAY-MONTH-YEAR

Participant ID # \_\_\_\_\_

Visit Date \_\_\_\_/\_\_\_\_/\_\_\_\_

## Visit 8: PROMIS – PAIN INTERFERENCE

To be completed by assessment team investigator

**Instructions:** Please respond to each item by marking one box per row.

In the past 7 days...

|                                                                                                              | Not at all | A little bit | Somewhat | Quite a bit | Very much |
|--------------------------------------------------------------------------------------------------------------|------------|--------------|----------|-------------|-----------|
| How much did pain interfere with your enjoyment of life?                                                     |            |              |          |             |           |
| How much did pain interfere with your ability to concentrate?                                                |            |              |          |             |           |
| How much did pain interfere with your day to day activities?                                                 |            |              |          |             |           |
| How much did pain interfere with your enjoyment of recreational activities?                                  |            |              |          |             |           |
| How much did pain interfere with doing your tasks away from home (e.g., getting groceries, running errands)? |            |              |          |             |           |

|                                                           | Never | Rarely | Sometimes | Often | Always |
|-----------------------------------------------------------|-------|--------|-----------|-------|--------|
| How often did pain keep you from socializing with others? |       |        |           |       |        |

Score: \_\_\_\_\_

**Investigator Signature:** \_\_\_\_\_

**Date:** \_\_\_\_\_

DAY-MONTH-YEAR

Participant ID # \_\_\_\_\_

Visit Date \_\_\_\_/\_\_\_\_/\_\_\_\_

## Visit 8: PROMIS – PHYSICAL FUNCTION

*To be completed by assessment team investigator*

Instructions: Please respond to each item by marking one box per row.

|                                                                                                                                         | Not at all | Very little | Somewhat | Quite a bit | Cannot do |
|-----------------------------------------------------------------------------------------------------------------------------------------|------------|-------------|----------|-------------|-----------|
| Does your health now limit you in doing vigorous activities, such as running, lifting heavy objects, participating in strenuous sports? |            |             |          |             |           |
| Does your health now limit you in walking more than a mile?                                                                             |            |             |          |             |           |
| Does your health now limit you in climbing one flight of stairs?                                                                        |            |             |          |             |           |
| Does your health now limit you in lifting or carrying groceries?                                                                        |            |             |          |             |           |
| Does your health now limit you in bending, kneeling, or stooping?                                                                       |            |             |          |             |           |

|                                                                              | Without any difficulty | With a little difficulty | With some difficulty | With much difficulty | Unable to do |
|------------------------------------------------------------------------------|------------------------|--------------------------|----------------------|----------------------|--------------|
| Are you able to do chores such as vacuuming or yard work?                    |                        |                          |                      |                      |              |
| Are you able to dress yourself, including tying shoelaces and doing buttons? |                        |                          |                      |                      |              |
| Are you able to shampoo your hair?                                           |                        |                          |                      |                      |              |
| Are you able to wash and dry your body?                                      |                        |                          |                      |                      |              |
| Are you able to get on and off the toilet?                                   |                        |                          |                      |                      |              |

Score: \_\_\_\_\_

Investigator Signature: \_\_\_\_\_

Date: \_\_\_\_\_

DAY-MONTH-YEAR

Participant ID # \_\_\_\_\_

Visit Date \_\_\_\_/\_\_\_\_/\_\_\_\_

## Visit 8: CHECKLIST - PHYSIOLOGICAL OUTCOMES

*To be completed by assessment team investigator*

### **Experiment 1. Muscular Effects**

- ☐ Ensure study participant is safe to enter a magnetic field.
- ☐ Have study participant lie supine for 30-minutes.
- ☐ Obtain and review scout images.
- ☐ Perform The RELIEF Study imaging protocol.
- ☐ Review images and ensure images are high quality.
- ☐ If necessary, repeat the imaging protocol and delete prior file.
- ☐ Save files to MRI terminal hard drive and back-up to cloud.

### **Experiment 2. Spinal Effects**

- ☐ Instrument study participant for EMG.
- ☐ Instrument study participant for motion capture.
- ☐ Perform The RELIEF Study short latency spinal reflex protocol
- ☐ Perform The RELIEF Study standardized reaching protocol.
- ☐ Perform The RELIEF Study trunk perturbation protocol.
- ☐ If necessary repeat a trial and delete prior file.
- ☐ Save files to lab secure network hard drive and back-up to cloud.

### **Experiment 3. Cortical Effects**

- ☐ Instrument study participant for EMG.
- ☐ Perform The RELIEF Study short latency spinal reflex protocol
- ☐ Map and mark the vertex of the skull.
- ☐ Find motor threshold.
- ☐ Perform The RELIEF Study paired pulse TMS protocol.
- ☐ Review signals throughout and ensure they are high quality.
- ☐ If necessary repeat a trial and delete prior file.
- ☐ Save files to lab terminal hard drive and back-up to cloud.

Did the participant complete the experiment?

☐ No

☐ Yes

Comments:

Investigator Signature: \_\_\_\_\_

Date: \_\_\_\_\_

DAY-MONTH-YEAR

Participant ID # \_\_\_\_\_

Visit Date \_\_\_\_/\_\_\_\_/\_\_\_\_

---

## VISIT 8: CHECKLIST

---

*To be completed by study coordinator*

1. Did the participant attend this visit? ☐ Yes (if yes, continue) ☐ No
2. Please check all assessments completed at this visit:
  - ☐ Prior and Concomitant Medications
  - ☐ Change in Medications
  - ☐ Health Status Reassessment
  - ☐ Contraindications for Lab Testing
  - ☐ Contraindications for Exposure to a Magnetic Field (if applicable)
  - ☐ NPR – Numeric Pain Rating
  - ☐ RMDQ - Roland Morris Disability Questionnaire
  - ☐ PROMIS – Pain Intensity
  - ☐ PROMIS – Pain Behavior
  - ☐ PROMIS – Pain Interference
  - ☐ PROMIS – Physical Function
  - ☐ Physiological Outcomes
3. Is the participant continuing in the study?
  - ☐ No (If no, remember to complete a STUDY COMPLETION form.)
  - ☐ Yes (If yes, schedule next visit.)

Comments:

---

**Investigator Signature:** \_\_\_\_\_

**Date:** \_\_\_\_\_

DAY-MONTH-YEAR

# Visit 9

Investigator Signature: \_\_\_\_\_

Date: \_\_\_\_\_

DAY-MONTH-YEAR

[figure not shown][figure not shown]

Case Report Forms  
Final Version 5.0  
21 April 2016

Participant ID # \_\_\_\_\_

Visit Date \_\_\_\_/\_\_\_\_/\_\_\_\_

## Visit 9: PRIOR AND CONCOMITANT MEDICATIONS

*To be completed by study coordinator*

Have you taken any medications (including over the counter pain relief medications) or used heat or ice for your back pain in the past 7 days?

☐ No ☐ Yes (If YES, record below.)

| Medication/Modality | Frequency and Dose | Indication | Start Date | Stop Date | Ongoing                  |
|---------------------|--------------------|------------|------------|-----------|--------------------------|
| 1.                  |                    |            |            |           |  |
| 2.                  |                    |            |            |           |  |
| 3.                  |                    |            |            |           |  |
| 4.                  |                    |            |            |           |  |
| 5.                  |                    |            |            |           |  |

Investigator Signature: \_\_\_\_\_

Date: \_\_\_\_\_

DAY-MONTH-YEAR

Participant ID # \_\_\_\_\_

Visit Date \_\_\_\_/\_\_\_\_/\_\_\_\_

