### 1.1 Mechanistic Component

The primary objective of the mechanistic component is to identify the physiological and biomechanical bases for changes in pain and disability associated with the respective interventions. As stated previously, participants will be recruited and enrolled into three separate experiments and then randomly assigned to one of three treatment arms. Additionally, for this objective we seek to determine the 1) acute effects of manual therapies, 2) the effects following a 3-week course of treatment, and 3) the sustained effects assessed approximately 1 month after completing the course of treatment. Thus, for this objective we will include 4 assessment points (baseline plus the 3 time points described above) for our physiological outcome measures. Below we outline the primary physiological outcomes for each group.

- Group 1 (Muscular Effects): Subjects assigned to this group will undergo a magnetic resonance imaging examination to quantify the skeletal muscle proton transverse relaxation time (T2) of the lumbar muscles.
- Group 2 (Spinal Effects): Subjects assigned to this group will undergo neurophysiological and biomechanical examinations to quantify short-latency stretch reflex excitability, trunk muscle onset latencies in response to postural perturbations, and lumbar motion during volitional movement tasks.
- Group 3 (Cortical Effects): Subjects assigned to this experiment will undergo a transcranial magnetic stimulation protocol to quantify motor evoked potential amplitude, intracortical facilitation, and short-interval intracortical inhibition.

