Study Duration: The study duration for an individual participant with low back pain is ~ 8 weeks. Specifically, we expect that the typical amount of time between the event of enrollment ascertainment and randomization will be 3-5 days (maximum 7), and that randomization will occur when study participants begin a study intervention (visit 2). The study intervention will occur over a 3-week period followed by approximately 4-week follow-up. Thus, in total the study duration for an individual participant will be ~ 8 weeks. Specifically, in the first visit we will obtain informed consent and conduct a screening exam to determine if candidates meet the inclusion/exclusion criteria for a given experiment. If subjects meet the inclusion/exclusion criteria for an experiment they will be enrolled into the study and allocated to one of three experimental measurement groups (i.e., Muscular, Spinal, or Cortical). At the second visit, participants will then be randomized to an intervention arm (i.e., mobilization, manipulation, or laser), baseline assessments of both clinical and physiological outcome measures will be obtained, a treatment intervention will be performed, and clinical and physiological outcome measures will be repeated (i.e., follow-up assessment). Participants will then undergo an additional five treatments over the next three weeks (visits 3-7; total treatments: 6; treatment frequency: 2x/week). It should be noted that following treatment 1 we will assess expectancy and credibility expectations for the respective treatment intervention. Three days +/- 1-day after the final treatment, subjects will report back to the laboratory for a follow-up assessment of the clinical and physiological outcome measures (visit 8). Lastly, to determine the long-term effects of the interventions, subjects will report back to the laboratory approximately 4 weeks (28-days +/- 4-days) after their last treatment for the final follow-up assessment of the clinical and physiological outcome measures.

(visit 9). The study duration for a participant in the healthy control group is 3-hour including screening, baseline assessments, and lab testing. The anticipated duration for the RELIEF Study is 5-years. We anticipate the total enrollment time to take up to 4 years (48 months). The required monthly enrollment rate for study completion in the proposed time frame is 3.4 subjects/month.

Randomization, Stratification, and Blinding:

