### **5.3.3 Prohibited Interventions**

- Narcotics
- Muscle relaxants
- Any treatment specific for low back pain delivered by a health practitioner (e.g., physician, physical therapist, chiropractor, massage therapist, or acupuncturist).

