- **Per-Protocol Analysis (PPA):** For the PPA we will exclude study participants who: 1) fail to attend 4 out of 6 treatment sessions; and 2) receive prohibited concomitant interventions (section 5.3.3), or 3) develop an exclusionary medical condition while on study protocol. Finally, we will assess how comparable estimated parameters vary between ITT and PPA analyses. Below we describe our analytic plans for specific outcome measures.

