## Visit 8: PRIOR AND CONCOMITANT MEDICATIONS

*To be completed by study coordinator*

Have you taken any medications (including over the counter pain relief medications) or used heat or ice for your back pain since your last visit?

☐ No ☐ Yes (If so, record below.)

Number Days since last Visit: \_\_\_\_\_

| Medication/Modality | Frequency and Dose | Indication | Start Date | Stop Date | Ongoing                  |
|---------------------|--------------------|------------|------------|-----------|--------------------------|
| 1.                  |                    |            |            |           |  |
| 2.                  |                    |            |            |           |  |
| 3.                  |                    |            |            |           |  |
| 4.                  |                    |            |            |           |  |
| 5.                  |                    |            |            |           |  |

Investigator Signature: \_\_\_\_\_

Date: \_\_\_\_\_

DAY-MONTH-YEAR

Participant ID # \_\_\_\_\_

Visit Date \_\_\_\_/\_\_\_\_/\_\_\_\_

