## Visit 9: CHANGE IN MEDICATION USE

*To be completed by study coordinator*

Have you had any changes in medication use NOT related to your back pain in the past 7 days?

☐ No ☐ Yes (If YES, record below.)

| Medication | Indication* | Dose & Frequency | Start Date | Stop Date | Ongoing                  |
|------------|-------------|------------------|------------|-----------|--------------------------|
| 1.         |             |                  |            |           |  |
| 2.         |             |                  |            |           |  |
| 3.         |             |                  |            |           |  |
| 4.         |             |                  |            |           |  |
| 5.         |             |                  |            |           |  |

\*If Indication is related to a negative change in health status, alert study coordinator, complete Health Status Reassessment and enter in Adverse Event Log.

Notes:

Investigator Signature: \_\_\_\_\_

Date: \_\_\_\_\_

DAY-MONTH-YEAR

Participant ID # \_\_\_\_\_

Visit Date \_\_\_\_/\_\_\_\_/\_\_\_\_

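### The Visit 9 form asks about back-pain drugs, heat and ice for only 7 of the 20 to 30 days since Visit 8, and no form at Visits 2 to 9 asks directly about practitioner care for the back, so the per-protocol exclusion for prohibited care cannot be applied reliably

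*Supplement*

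**What the plan says.** The Prior and Concomitant Medications form (Case Report Forms v5.0) asks at Visits 3 to 8 whether the participant has taken medications "or used heat or ice for your back pain since your last visit". At Visit 9 the look-back shortens: "or used heat or ice for your back pain in the past 7 days". The companion form, Change in Medication Use, covers the same 7 days and only other drugs: "Have you had any changes in medication use NOT related to your back pain in the past 7 days".

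Section 3 places Visit 8 "Three days +/- 1-day after the final treatment" and Visit 9 "approximately 4 weeks (28-days +/- 4-days) after their last treatment". Visit 9 is OA4, which serves the third aim of the mechanistic component in section 1.1, "the sustained effects assessed approximately 1 month after completing the course of treatment".

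Section 5.3.3 prohibits narcotics, muscle relaxants and "Any treatment specific for low back pain delivered by a health practitioner". The per-protocol paragraph of section 9.5 excludes participants who "receive prohibited concomitant interventions (section 5.3.3"), and deviation code D5 exists for unallowable concomitant treatment.

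The prescreen questionnaire and the Visit 1 back-pain history both ask about treatment for the back in the past month. No form shown for Visits 2 to 9 repeats that question.

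**The concern.** The look-back is shortest, relative to the interval it should cover, at the visit that follows the longest gap in the schedule. A narcotic or muscle relaxant taken in the first weeks after Visit 8 and stopped more than 7 days before Visit 9 would not be recorded by the form meant to find it. A course of chiropractic, physical therapy or massage at any time after screening is asked about by no form directly.

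Two uses of the data depend on this information. The first is the per-protocol set, because a stated exclusion has no routine source of data. The second is the reading of OA4. Section 9.1 includes OA4 in every mechanistic primary hypothesis, and by then study treatment has ended. Participants with persisting pain then have most reason to look for other care. If that happened more in one arm, the OA4 contrast would partly reflect it, and the trial could not show whether it had happened.

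**Working it through.** The plan states no figure for this point, so there is none to reproduce. The check is window arithmetic plus a comparison of forms.

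**Interval between Visits 8 and 9** (section 3; days counted from the last treatment, Visit 7):
- Visit 8: 3 ± 1, so day 2 to 4. Visit 9: 28 ± 4, so day 24 to 32.
- Shortest gap: 24 − 4 = 20 days. Longest gap: 32 − 2 = 30 days.
- Time off treatment (Visit 7 to Visit 9) is a different quantity: 24 to 32 days.

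**Share not covered by a 7-day look-back:**
- 20-day gap: 20 − 7 = 13 days; 13/20 = 65%.
- 30-day gap: 30 − 7 = 23 days; 23/30 = 77%.

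**Other windows in section 6.2.4:**
- Physiological outcomes at 3 ± 2 and 28 ± 4 days: gap 24 − 5 = 19 to 32 − 1 = 31 days, leaving 12 to 24 days (63 to 77%).
- Clinical outcomes at study days 23–25 and 57–61: gap 57 − 25 = 32 to 61 − 23 = 38 days, leaving 25 to 31 days (78 to 82%).
- With Visit 7 on day 21, 3 ± 1 gives days 23–25 as stated, but 28 ± 4 gives days 45–53, not 57–61. These passages need reconciling. The conclusion here is the same under each.

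**What each Visit 9 form can pick up:**
- Prior and Concomitant Medications: back-pain drugs, heat and ice in the last 7 days. A drug still in use is logged with its start date; one stopped earlier is not.
- Change in Medication Use: drugs unrelated to back pain, last 7 days.
- Health Status Reassessment: the whole interval since Visit 8, with a treatment field, but only after a reported change in health. A participant with unchanged chronic pain who sees a chiropractor can truthfully answer no.
- Contraindications for Lab Testing: benzodiazepines, in Experiment 3 only.

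**Scale of possible bias, for orientation only.** Bias = (difference between arms in the proportion receiving effective outside care) × (effect of that care). The documents give neither term. Assuming an effect of 2 NPR points and differences of 5, 10 and 15 percentage points, the bias is 0.1, 0.2 and 0.3 points, or 0.04, 0.08 and 0.12 of the NPR standard deviation of 2.5 in section 9.2. Nothing comparable can be computed for T2, reflex or TMS outcomes.

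**The case against.** **The 7-day window has a rationale.** Visit 2 uses the same 7-day wording, and the pain rating at Visits 2 and 9 also asks about the last 7 days. At Visits 3 to 8 both the medication item and the pain item refer to the time since the previous visit. So at OA4 the medication look-back matches the pain-recall window and the baseline form. This stands as a reason to keep a 7-day item. It does not supply what the per-protocol exclusion needs, which is exposure over the whole interval. At entry, section 4.2 applies 30 days to narcotics, muscle relaxants and spinal manual therapy.

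**Capture is partial, not absent.** A reader might infer that outside care goes wholly unseen. The documents do not support that: the Health Status Reassessment has a treatment field, ongoing drugs carry start dates, and code D5 can be used if staff learn of outside care. The Visit 1 consent record also shows that participants are told to limit back-pain relief to heat, ice and over-the-counter drugs, beside the statement of nine visits over two months. What is missing is a systematic question.

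**Reach is limited.** The RCT primary endpoint is OA3, which the Visit 9 form cannot affect, and the RCT comparisons at OA4 are exploratory. Intention to treat is the primary method and keeps these participants whatever is asked. All of this stands. The practitioner-care gap, however, covers Visits 3 to 8 too, so it touches the per-protocol analysis at OA3.

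**Version and timing.** The forms shown are v5.0. The correspondence on protocol version 6.0 says the electronic forms were modified, and those are not shown. It also describes the study as almost complete for participants with back pain, and the appendix reports 18 + 31 = 49 of 60 tested in Experiment 2. The point therefore holds for the forms shown, and a late change has a cost.

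**Conclusion.** The point holds as a data-capture gap. On the v5.0 forms, 13 to 23 of the 20 to 30 days before Visit 9 (65 to 77%) are not asked about for back-pain drugs, heat and ice, and practitioner care for the back is not asked about directly at any of Visits 2 to 9. The per-protocol exclusion for prohibited care cannot be applied reliably: misclassification is possible at OA4 for drugs and at OA3 and OA4 for practitioner care. Outside care cannot be compared between arms when sustained effects are interpreted.

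A reader might go further and infer that the sustained-effect results are contaminated, or that a true difference from sham would be reversed. The documents do not show this. They contain no rate of outside care, no evidence of imbalance between arms and no effect size for such care, so the direction and size of any bias are unknown. The day counts rest on the section 3 windows; the verdict also assumes that the version 6.0 electronic forms did not already change these items.

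**What to change.** 1. On the Visit 9 Prior and Concomitant Medications form, ask about the whole interval since the previous visit, as at Visits 3 to 8. The 7-day item can stay alongside it to match the pain-recall window. Coverage of the interval rises from 23–35% to 100%.
2. At Visits 3 to 9 add one yes/no item, with type and date: any treatment for the back from a health practitioner outside the study since the previous visit. Route positive answers to deviation code D5 and to the second per-protocol exclusion.
3. In section 9.5, state the period over which prohibited care counts towards the exclusion at each time point. Section 5.3.3 gives no end date, and the consent record only suggests that the restriction runs to Visit 9.
4. Report outside care by arm and visit interval beside the OA3 and OA4 results.

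Keep intention to treat primary. Do not rely on an analysis that simply drops participants with outside care: it conditions on an event after randomisation, and if poor responders seek more care it removes them selectively.

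The cost is small: two lines of form wording, a minor amendment and slightly longer recall at Visit 9. If the change comes late in enrolment, participants will fall under two recall windows; record the form version used so that this can be shown.
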